## Abstract

**Background:**

Mandibular distraction osteogenesis (MDO) is a major part of the treatment for hemifacial microsomia patients. Due to the narrow surgical field of the intraoral approach, osteotomy accuracy is highly dependent on the surgeons’ experience. Electromagnetic (EM) tracking systems can achieve satisfying accuracy to provide helpful real-time surgical navigation. Our research team developed an EM navigation system based on artificial intelligence, which has been justified in improving the accuracy of osteotomy in the MDO in animal experiments. This study aims to clarify the effect of the EM navigation system in improving the MDO accuracy for hemifacial microsomia patients.

**Methods:**

This study is designed as a single-centered and randomized controlled trial. Altogether, 22 hemifacial microsomia patients are randomly assigned to the experiment and control groups. All patients receive three-dimensional CT scans and preoperative surgical plans. The EM navigation system will be set up for those in the experiment group, and the control group will undergo traditional surgery. The primary outcome is the surgical precision by comparing the osteotomy position of pre- and postoperative CT scan images through the Geomagic Control software. The secondary outcomes include mandibular symmetry (occlusal plane deviation angle, mandibular ramus height, and body length), pain scale, and complications. Other indications, such as the adverse events of the system and the satisfactory score from patients and their families, will be recorded.

**Discussion:**

This small sample randomized controlled trial intends to explore the application of an EM navigation system in MDO for patients, which has been adopted in other surgeries such as orthognathic procedures. Because of the delicate structures of children and the narrow surgical view, accurate osteotomy and protection of nearby tissue from injury are essential for successful treatment. The EM navigation system based on artificial intelligence adopted in this trial is hypothesized to provide precise real-time navigation for surgeons and optimally improve patient outcomes, including function and aesthetic results. The results of this trial will extend the application of new navigation technology in pediatric plastic surgery.

**Trial registration:**

Chinese Clinical Trial Registry ChiCTR2200061565. Registered on 29 June 2022.

## Introduction

### Background and rationale {6a}

Hemifacial microsomia (HFM) is the second most common congenital dysplasia of the face after cleft lip and palate, with a prevalence of 1:3000–5000 live births [1]. The patients present asymmetric structures derived from first and second branchial arches, including hypoplastic mandible resulting in the deficit of muscles of mastication except for the masseter, deformed auricle/microtia/ anotia, and some patients even may have microphthalmia [1, 2]. It was reported that 49–100% of patients suffer mandibular hypoplasia, and patients may have mild hypoplasia or lack of temporomandibular joint (TMJ) [1]. The wildly adopted Pruzansky classification helps describe mandibular deformity [3].

Mandibular distraction osteogenesis (MDO) was popularized by McCarthy in 1992 to treat mandibular hypoplasia [2, 4]. In the MDO procedure, a single osteotomy occurs at the mandible ramus through the medial and lateral cortices in the space between the mandibular angle. The distraction forces are applied by a device fixed by screws on either side of the osteotomy line [4].

Planning the osteotomy plane is critical to avoid the injury of tooth roots, the inferior alveolar nerve, and the marginal mandibular branch of the facial nerve. It is also vital to the distraction vector for successful MDO and the final aesthetic result [5]. However, most of this procedure has been done intraoral. The narrow view and operative space of MDO in young patients increase the surgeons’ difficulty in achieving precise osteotomy. The development of versatile computer-assisted equipment and methods helps surgeons to locate the osteotomy during the procedure [4–7].

Our previous research adopted a computer-aided-designed (CAD) surgical guide to locate the osteotomy line during the surgery [5]. While the surgical guide has been designed preoperatively based on the patient’s CT scan and surgical simulation, the surgeons must put it on to the ramus in the narrow intraoral surgical incision, which is difficult, especially for very young children, and often needs to expand the incision which may cause extra injury. Therefore, navigation systems are invented as a great alternative to improve accuracy [7–10].

In recent years, scads of studies have reported that electromagnetic (EM) tracking systems can achieve satisfying accuracy. The EM sensors are usually small and delicate, allowing more free movement between the sensors and the generator [6]. Our team has developed a maxillofacial surgical robot system (MSRS) based on artificial intelligence surgical stimulation and EM navigation technology, which has been proven feasible for mandibular angle osteotomy in animal experiments in terms of accuracy and workflow of the procedure [11, 12]. Therefore, we proposed the MSRS system to clinical practice for hemifacial microsomia patients to explore the value of this system in improving the accuracy of osteotomy for our young patients.

## Objectives {7}

The primary objective of this trial is to assess the accuracy of electromagnetic (EM) tracking systems based on artificial intelligence in osteotomy for HFM patients, which is evaluated by measuring the difference in osteotomy between preoperative stimulated surgery and postoperative CT scan. The secondary goal of this trial is to assess the effect of adopting this system on improving the symmetry of the mandible, the postoperative pain score, the complication rate, and the satisfaction rating.

## Trial design {8}

This trial is a prospective randomized controlled trial. There are two parallel groups, including the experimental group of patients receiving the EM navigation system based on the artificial intelligence for osteotomy and the control group having the MDO surgery in a traditional method that surgeons perform the osteotomy on their own experience. The allocation ratio of the two groups is 1:1. The framework of this trial is shown in Fig. 1.

**Fig. 1 Fig1:**
[figure not shown]
The trial framework. HFM, hemifacial microsomia; MDO, mandibular distraction osteogenesis

## Methods: participants, interventions, and outcomes

### Study setting {9}

The candidate HFM patients enrolled in this trial are from Shanghai 9th People’s Hospital, School of Medicine, Shanghai Jiao Tong University. It is an academic hospital featured in plastic and reconstructive surgery. This trial has been registered in the Chinese Clinical Trial Registry Center (ChiCTR) with the number ChiCTR2200061565. (http://www.chictr.org.cn/edit.aspx?pid=168053&htm=4).

### Who will take informed consent? {26a}

A specific investigator from the medical team will obtain written consent from the parents of the HFM patients who agree to participate.

### Additional consent provisions for collection and use of participant data and biological specimens {26b}

Not applicable, as no biological specimens would be collected.

### Interventions

#### Explanation for the choice of comparators {6b}

The patients of the control group received the mandibular distraction osteogenesis (MDO) surgery traditionally, in which the surgeon performs the osteotomy on their own experience based on preoperative design without navigation equipment. That is the most widely used method in the current operating theater.

#### Intervention description {11a}

After obtaining the consent form, all patients of each group receive the preoperative 3D CT scan, and the data will be stored in DICOM format and imported into the corresponding processing software (Mimics 21.0, Materialise, Belgium). The surgeons adopt the Mimics software to reconstruct the mandibular and design the osteotomy line to avoid the inferior alveolar nerve inside the mandibular as in the preoperative plan (Fig. 2).

**Fig. 2 Fig2:**
[figure not shown]
Preoperational surgical design is shown in Mimics (experiment group). **a** Design of osteotomy. **b** Design of distractor fixation. The position of the distractor is based on the osteotomy line. Orange: the proximal segment of the mandibular ramus. Blue: the distal segment of the mandible. Red: dental splint. Purple: robotic end with the template. Cyan: bone saw. Yellow: the distractor

For the control group, the surgeon locates the osteotomy line on the mandibular on their own experience based on the preoperative design image without the navigation, which is a traditional procedure of MDO for HFM patients.

For the experiment group, the patients receive the preoperative CT scan equipped with a customized dental splint made based on the patient’s dental mold and assembled with four steel spheres with a diameter of 2 mm as the magnetic field tracking targets to navigation (Fig. 3a, b). Their preoperative plans generated by the Mimics software are transferred to the navigation system, which also stores the location information generated by the steel spheres of the dental splint. Besides, a 3D printed template is generated based on the designed osteotomy plan.

**Fig. 3 Fig3:**
[figure not shown]
Robotic navigation-assisted MDO. **a** Surgical environment. **b** Verification of the system registration. The verification pinpointing at the registration point on the splint represents accurate registration. **c** Template in position. The surgeon is conducting osteotomy with the saw blade relying on the template. **d** Assisted osteotomy from the intraoral viewpoint. (A) Navigation system. (B) Computer base. (C) Dental splint. (D) Verification pin. (E) Electromagnetic receptor. (F) Electromagnetic generator. (G) Bone saw. (H) Template arriving at the designed osteotomy line

Before the osteotomy, the splint is mounted on the patient’s teeth as the registration piece is connected to the magnetic field of the navigation system. The 3D printed template will be clamped on the end of the robotic arm to locate precisely the osteotomy line according to the preoperative design documents stored and managed by the EM system. Then, the surgeon performs the osteotomy by moving the saw along the template (Fig. 3c, d).

The management of all patients is identical, and to reduce surgical bias, the chief surgeon in the control and experimental groups will be the same senior craniomaxillofacial specialist with more than 15 years of specialty practice and an average annual craniofacial surgery volume of 300 or more. There will be two attending surgeons assisting with the operation. The team training of the navigation-assisted surgery group is more than 100 h.

#### Criteria for discontinuing or modifying allocated interventions {11b}

The criteria for discontinuing or modifying include the malfunction of the EM system, surgical accident, and any situation that makes the surgeon need to finish the surgery as soon as possible. The patients’ demographic data that meet those criteria will still be collected.

#### Strategies to improve adherence to interventions {11c}

To improve retention, the participants will get a stipend if they return to the hospital for follow-up on time. In this study, children received surgical treatment with the participation of computer-assisted surgery, which reduced the surgical risks and complications. The distraction effect is evident in the early stage, which is conducive to the psychological development of school-age children. Some guardians worry that premature surgery is not conducive to nursing, and other psychological relief can also be alleviated. In addition, scientific research expenses are subsidized to reduce part of the economic burden.

#### Relevant concomitant care permitted or prohibited during the trial {11d}

There is no specific concomitant care or interventions prohibited during the trial. The two groups’ patients will receive standard perioperative care for their conditions.

#### Provisions for post-trial care {30}

After the trial, the surgical team will provide standard postoperative medical care for the participating patients.

### Outcomes {12}

#### Primary outcome

The primary outcome will be the accuracy of osteotomy by comparing the preoperative design and postoperative CT. The two mental foremen and the condylion of the unaffected side are marked as the registration points. Altogether, 10 points on the osteotomy plane of each pre- and postoperative CT scan are selected to calculate the accuracy (Fig. 4a). Each patient’s data will be measured three times to avoid measurement bias, and the staff responsible for measurement are blinded to the patient’s grouping information.

**Fig. 4 Fig4:**
[figure not shown]
Postoperative imaging analysis. **a** Accuracy analysis by comparing the CT data 1 week after MDO with the preoperative design. **b** Symmetry analysis by comparing the image after removing the distractor with the original CT

#### Secondary outcomes

The secondary outcome includes the symmetry of the mandibular, pain scale, recording of surgical complications, and satisfactory score.

The symmetry of the mandibular is evaluated by three indicators: the angle of inclination, the mandibular ramus’s height, and the mandibular body’s length, which will be obtained from the CT 6 months after the surgery (Fig. 4b).

The angle of inclination: A horizontal plane (HP) is established by selecting bilateral suborbital points (Or) and the healthy superior external auditory canal points (Po). Establish the occlusal plane (OP) from the adjacent medial point of the maxillary central incisor to the medial buccal cusp of the bilateral first molar. Measure the angle between the occlusal plane and the horizontal plane, set as angle A. The smaller angle A indicates the smaller deviation angle of the mandible and maxilla, meaning the better symmetry of the lower face.

The height of mandibular ramus: The height of mandibular rami, that is, the distance between condylion (Co) and mandibular gonion (Go), is measured respectively. The distance of the affected side is set as *h*, and the distance of the healthy side is set as *H*. Comparing the values of the affected and the healthy sides. The smaller the difference, the better the bilateral symmetry.

The length of the mandibular body: The menton (me) is marked, and the length of the bilateral mandibular body, the distance from the bilateral gonion (Go) to the menton (Me), is measured respectively. The distance of the affected side is set as *l*, and the distance of the healthy side is set as *L*. Comparing the values of the affected and the healthy sides, the smaller the difference, the better the bilateral symmetry.

The pain scale: The evaluation time is 1 week, 1 month, and 6 months after surgery. The pain scale is an international visual analog scale, with a scale from 0 to 10 representing no pain to the most intense pain.

The postoperative complications during the trial will be recorded, including local infection, bone nonunion, scar hyperplasia, occlusal disorder, nerve injury, and tooth germ injury.

The satisfaction score was evaluated by a modified 5-point Likert table, with 1–5 indicating unsatisfactory to very satisfied. It will be recorded at the 1-week, 1-month, and 6-month follow-up.

Besides, the preoperative data are recorded, including surgical time, system installation time, hospital stay, blood loss volume, drainage volume, and drainage duration.

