## Data collection and management

### Plans for assessment and collection of outcomes {18a}

The image data from the preoperative and postoperative procedures will be transferred into Geomagic Control X (3D System, SC). The accuracy of the osteotomy plane is assessed after the registration.

The accuracy of the osteotomy between the preoperative plan and the postoperative result will be the primary outcome measure. The postoperative CT will be performed within 7 days following surgery, which is the most critical outcome for determining the efficacy of robotic navigation technology. Improvements in the symmetries of the mandibles will be assessed by comparing the CT 6 months after MDO and the preoperative ones with Mimics.

It will be organized for surgeons to record important information after surgery during the follow-up period for security measures such as intraoperative blood loss, operation time, hospitalization, possible blood transfusion, and complication rates.

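### Angle A, the full angle between the occlusal and horizontal planes, mixes front-back tilt with left-right cant, so a smaller A need not mean better symmetry

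*Protocol article*

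**What the plan says.** The protocol article, under Secondary outcomes, states: "The symmetry of the mandibular is evaluated by three indicators: the angle of inclination, the mandibular ramus’s height, and the mandibular body’s length". The first of these, the angle of inclination, is built in three steps.

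- Reference plane: "A horizontal plane (HP) is established by selecting bilateral suborbital points (Or) and the healthy superior external auditory canal points (Po").
- Occlusal plane: drawn "from the adjacent medial point of the maxillary central incisor to the medial buccal cusp of the bilateral first molar".
- Measurement: "Measure the angle between the occlusal plane and the horizontal plane, set as angle A".

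The interpretation follows directly: "The smaller angle A indicates the smaller deviation angle of the mandible and maxilla, meaning the better symmetry of the lower face".

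The abstract lists the same measure under "mandibular symmetry (occlusal plane deviation angle, mandibular ramus height, and body length"). The Secondary outcomes section takes the indicators from the 6-month CT. The section on assessment and collection of outcomes {18a} adds a before-and-after comparison: "Improvements in the symmetries of the mandibles will be assessed by comparing the CT 6 months after MDO and the preoperative ones with Mimics". The text nowhere mentions a frontal projection or a separate left-right component of A.

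**The concern.** The occlusal plane is fixed by one point at the front and two at the back, so it can tilt in two ways relative to the horizontal plane. It can pitch (front to back) or cant (left to right). Only cant is a left-right asymmetry. The plane-to-plane angle combines the two, so A is positive for any face with some pitch, however symmetric it is.

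Two things are at stake. First, a real correction of cant is compressed in A even when pitch does not change. Second, any difference in pitch between patients, or between one patient's two scans, enters A as if it were asymmetry. With 11 patients planned per group, a compressed effect plus irrelevant variance could leave the result on this indicator uninterpretable. The other two indicators, ramus height and body length, are differences between the affected and healthy sides and do not share the problem.

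**Working it through.** The protocol states no figure for A, so there is none to reproduce. The check is geometric.

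**Inputs**
- Horizontal plane: both Or points and the healthy-side Po (Secondary outcomes).
- Occlusal plane: the incisor point and the two first-molar cusps (Secondary outcomes).
- Pitch p and cant r: not given in the protocol. Assumed for illustration: p from 0° to 15°, r from 0° to 8°.

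**Formula.** Rotate the occlusal plane by p about the left-right axis and by r about the front-back axis. The angle between its normal and the normal of the horizontal plane satisfies

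cos A = cos p × cos r,

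which for small angles is approximately A = √(p² + r²). Building the plane from three points, rotating it and measuring the angle numerically gives the same values.

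**1. A level face does not score zero.** With r = 0, A = p, so A is 5°, 10° or 15° at pitch 5°, 10° or 15°.

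**2. A true 4° correction of cant (6° to 2°), pitch constant**

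| Pitch | A at cant 6° | A at cant 2° | Change in A | Share of the 4° lost |
|---|---|---|---|---|
| 0° | 6.00° | 2.00° | 4.00° | 0% |
| 5° | 7.80° | 5.38° | 2.42° | 1.58/4 = 40% |
| 10° | 11.65° | 10.20° | 1.45° | 2.55/4 = 64% |
| 15° | 16.13° | 15.13° | 1.00° | 3.00/4 = 75% |

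**3. Two faces with different pitch**
- Level face, p = 10°, r = 0°: A = 10.0°.
- Canted face, p = 5°, r = 8°: A = 9.4°.

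The stated rule scores the canted face as the more symmetric.

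**4. One face at two scans.** Suppose cant improves from 6° to 2° while pitch moves from 8° to 10°. Then A goes from 9.99° to 10.20°, and a real correction reads as a slight worsening.

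**5. The alternative measure.** Take the angle between the inter-molar line and the horizontal plane, arcsin(height difference between the two cusps / distance between them). It is 0° for a level line at any pitch, provided the cusps sit at the same front-back position.
- If pitch is applied before cant, the measure equals r exactly, and the 6° to 2° correction reads as 4.00°.
- If cant is applied before pitch, it equals arcsin(sin r × cos p). At p = 15° this is 5.80° and 1.93°, a change of 3.86°.

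The correction therefore registers as 3.86° to 4.00° over the whole assumed pitch range.

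**The case against.** The strongest reply has five parts.

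- **The figure.** Fig. 4b illustrates the symmetry analysis, is not shown here, and may depict a frontal-view angle. The names given to the measure also suggest that cant was intended. This is fair as to intent. But the text defines the angle between the planes, and if the figure shows something else, the text still needs correcting.
- **Fixed pitch.** At any fixed non-zero pitch A rises with cant, so A is not empty of information. If a patient's pitch is stable between the preoperative and 6-month scans, the direction of change is right. This stands. The rule as written is not limited to fixed pitch, however. The compression remains when pitch is constant, and taking A from the 6-month CT allows faces with different pitch to be compared.
- **Randomisation and blinding.** Pitch should balance between arms on average, so the expected harm is noise and dilution, not a systematic advantage for one arm. This also stands, but randomisation removes neither the noise nor the dilution.
- **Assumed magnitudes.** Pitch and cant are not in the protocol, and at zero pitch there is no loss. This is true, and it is why a range is shown. The direction of the result holds for any non-zero pitch.
- **The alternative is not perfect.** If the inter-molar line is yawed, some pitch leaks in. With zero cant, 10° yaw and 10° pitch, it reads arcsin(sin 10° × sin 10°) ≈ 1.7°. For the same face A reads 10°, so the alternative is still much closer to the true cant of zero.

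**Conclusion.** The concern holds. As written, A is not a measure of left-right symmetry, and the rule that a smaller A is better fails whenever pitch differs between the faces or scans compared. Over an assumed pitch of 5° to 15°, between 40% and 75% of a 4° correction of cant disappears from A even if pitch never changes. A level face can also score worse than one with 8° of cant. These sizes depend on the assumed angles; the geometry does not.

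The consequence is limited to one of three indicators of one secondary outcome. It should be corrected before analysis, but it does not threaten the trial's main conclusion.

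**What to change.** Redefine the angle of inclination in the Secondary outcomes section as the absolute angle between the line joining the left and right first-molar cusps and the horizontal plane, computed as the arcsine of the left-right height difference (measured perpendicular to the horizontal plane) divided by the inter-cusp distance. Keep the statement that smaller is better for this quantity only. Drop the full plane-to-plane angle as a symmetry measure, or report it descriptively. Bring the abstract's wording and Fig. 4b into line with the new definition.

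The cost is a change of wording and a recalculation from landmarks already marked on the CT. No new scan, landmark or patient is needed. The small sensitivity to yaw noted above can be acknowledged in one sentence.
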